### Blinding

2.5

In this study, as the administration of the first dose of PS depends on the initial lung ultrasound results, ultrasound physicians and neonatologists will be informed of the infant's group assignment at the beginning. However, subsequent ultrasound results after the first dose will not be disclosed to the clinical team to prevent any influence on the assessment of indications for the second dose of PS. In addition, blinding will be implemented for the members involved in outcome assessment and data analysis to reduce bias.

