Clinical diagnostic criteria for NRDS: Within 24 h of birth, if an infant experiences respiratory distress, they are supported with nasal intermittent positive pressure ventilation (NIPPV) or nasal continuous positive airway pressure (NCPAP). Diagnosis of NRDS occurs when the infant exhibits progressively worsening symptoms, such as a respiratory rate of more than 60 breaths/min, grunting, nasal flaring, intercostal retractions, and/or cyanosis, along with a peripheral capillary oxygen saturation (SpO2) of 85% or less, a Silverman Anderson Score (SAS) of more than 5, or an hourly increase in SAS by more than 2 while the FiO_2_ is more than 0.4 (or >0.3 for those with a GA<28 weeks). These symptoms may or may not be accompanied by typical chest x-ray findings.

Indications for repeated use of PS include the following: within 72 h after birth (that is, 10–70 h after the initial PS administration), if respiratory distress persists, chest x-ray findings confirm the diagnosis of NRDS, and other causes of respiratory difficulties have been excluded.

Indications for endotracheal intubation and invasive mechanical ventilation within 72 h after birth include: (1) severe respiratory acidosis indicated by blood gas analysis 2 h after the initial PS administration (PaCO2 >65 mmHg, pH <7.20); (2) hypoxemia, with an FiO_2_ of more than 0.4 and an SpO2 of less than 0.85; (3) recurrent episodes of respiratory pauses, more than 3 episodes of spontaneously recoverable respiratory pauses per hour, or one episode of respiratory pause requiring positive pressure ventilation within 24 h; (4) an increase in SAS by more than 2 per hour, or an SAS of more than 5 persisting for more than 2 h; (5) pulmonary hemorrhage; (6) respiratory or cardiac arrest requiring endotracheal intubation for resuscitation; and (7) required by NICU physicians for respiratory support to ensure the infant will receive optimal treatment. Criteria for extubation include an FiO_2_ of less than 0.3 and a mean airway pressure (MAP) of less than 7–8 cmH2O.

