Criteria for discontinuation of non-invasive ventilation: (1) more than 72 h after birth; (2) a PEEP of 3–5 cmH2O or less during NCPAP, or an MAP of less than 6–7 cmH2O during NIPPV; (3) an FiO_2_ of 25% or less; (4) an SAS of less than 3; and (5) absence of respiratory pauses or bradycardia requiring stimulation for recovery. If all five conditions are met and sustained for over 24 h, discontinuation of non-invasive ventilation may be considered based on clinical assessment. If any of the following conditions arise after discontinuation of non-invasive ventilation, encompassing: (1) an FiO_2_ of more than 0.25 and an SpO2 of less than 85%; (2) an SAS of more than 3; or (3) three or more episodes of spontaneously recoverable respiratory pauses or bradycardia within 24 h, non-invasive ventilation will be reinstated. Reassessment for discontinuation of non-invasive ventilation will not be conducted until at least 48 h later.

All study participants will receive caffeine citrate within 24 h after birth to prevent respiratory pauses, with an initial loading dose of 20 mg/kg and a maintenance dose of 5–10 mg/kg per day.

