### Outcome measures

2.9

The primary outcome measure for this study is the duration of mechanical ventilation (both invasive and non-invasive) during hospitalization in the ultrasound and control groups. Secondary outcome measures encompass: (1) the utilization rate of PS in both groups; (2) the proportion of infants receiving the first dose of PS early (within 3 h after birth) and the time from birth to the initial PS administration; (3) the oxygen concentration and the worst oxygenation index (OI) at different time points following PS administration; (4) LUS at various intervals following PS administration (at 3 days, 7 days, 14 days, 28 days, and before discharge/at 36 weeks CA; and (5) the incidence rates of major complications in preterm infants such as BPD, intraventricular hemorrhage (IVH), retinopathy of prematurity (ROP), and necrotizing enterocolitis (NEC).

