### Sample size calculation

2.12

With the duration of mechanical ventilation as the primary outcome measure for both groups, we anticipate that patients in the conventional treatment group will require an average of 96 ± 12 h of respiratory support based on previous departmental data. It is expected that integrating ultrasound diagnosis will promptly improve respiratory function, reducing the mechanical ventilation duration to an average of 86 ± 12 h. To compare the difference in mechanical ventilation duration between the groups, a two-sample independent *t*-test will be employed, setting α at 0.05 and ensuring a power of 80%. With a 1:1 ratio between the groups, sample size estimation using PASS15 indicates that each group will require 24 patients, totaling 48 patients. Considering the potential risk of underestimating sample size due to low effect size and dropout rates, the actual sample size will be 60 patients (48 ÷ 80% = 60), with 30 patients in each group.

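### Clinicians who know the arm end the ventilation hours that form the primary outcome, under a rule with ranged MAP limits and no latest decision time; the stated blinding does not reach that decision

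*Protocol article*

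**What the plan says.** - **Outcome.** Section 2.9 defines the primary outcome as the "duration of mechanical ventilation (both invasive and non-invasive) during hospitalization".
- **Who knows the arm.** Under section 2.5, "ultrasound physicians and neonatologists will be informed of the" allocation at the start.
- **Safeguards.** Scan results after the first surfactant dose are kept from the clinical team. Section 2.5 gives the second dose as the reason; the limitations in section 3 refer more widely to later treatment. In addition, "blinding will be implemented for the members involved in outcome assessment and data analysis to reduce bias".
- **Stopping non-invasive support (section 2.8).** Five conditions must hold: age above 72 h; "a PEEP of 3–5 cmH2O or less during NCPAP, or an MAP of less than 6–7 cmH2O during NIPPV"; FiO2 at or below 25%; a Silverman Anderson score (SAS) under 3; and no pauses or bradycardia needing stimulation. When all have lasted over 24 h, "discontinuation of non-invasive ventilation may be considered based on clinical assessment". After support has been restarted, "Reassessment for discontinuation of non-invasive ventilation will not be conducted until at least 48 h later".
- **Extubation (section 2.8).** FiO2 below 0.3 and "a mean airway pressure (MAP) of less than 7–8 cmH2O".
- **Planning values (section 2.12).** The control arm is expected to need "an average of 96 ± 12 h of respiratory support" and the ultrasound arm 86 ± 12 h, with 30 infants per arm.

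**The concern.** The outcome ends when a clinician takes the infant off support. That clinician knows the arm, and the rule leaves two kinds of room that both comply with the protocol.

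1. **When the conditions count as met.** On NIPPV, an infant at a MAP of 6.5 cmH2O passes if the limit is read as 7 and fails if it is read as 6. The extubation limit has the same form, though it affects total hours only indirectly, because an extubated infant may remain on non-invasive support that still counts. The PEEP wording is best read as 5 or less but should say so.
2. **How long support continues afterwards.** Stopping is optional once the conditions have held. Every waiting time is a minimum, none is a maximum, and the rule asks for no reason if support goes on.

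If either kind of room is used differently in the two arms, the difference enters the primary comparison as if it were a treatment effect. It could create a false difference or hide a real one.

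**Working it through.** **The plan's own figure.** With a difference of 10 h, SD 12 h, two-sided α of 0.05 (sidedness is not stated; two-sided assumed) and 80% power, the exact t calculation gives 23.6, so 24 per arm, with power 80.7%. Then 48 ÷ 0.8 = 60. The stated sample size reproduces. Power at 30 per arm is 88.8%.

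**How small a shift matters.** At 30 per arm the smallest significant difference is 2.00 × 12 × √(2/30) ≈ 6.2 h. That is well under the 24 h window in the stopping rule itself.

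**Do the safeguards reach the stopping decision?**

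| Safeguard | Acts on | Acts on the stopping decision? |
|---|---|---|
| Later scans withheld | What clinicians know about the lung after the first dose | No; the arm is still known |
| Blinded assessors and analysts | Recording and analysis of hours | No; the hours are already set at the bedside |

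**Sensitivity to differential delay.** The length of delay, the share of infants affected and the arm are all assumptions. Let a share p of one arm be delayed by D hours. The mean of that arm rises by pD and its variance becomes SD² + D²p(1−p).

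False positives, with no true effect, SD 12 and D = 24 in controls only:
- p = 0.25: shift 6 h; variance 144 + 576 × 0.25 × 0.75 = 252; SE = √((144 + 252)/30) = 3.63; 6/3.63 = 1.65; rejection about 0.38.
- p = 0.10: shift 2.4 h; variance 144 + 576 × 0.10 × 0.90 = 195.84; SE = √((144 + 195.84)/30) = 3.37; 2.4/3.37 = 0.71; rejection about 0.11.

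Simulation (40,000 trials per cell, normal data, 30 per arm, two-sided t-test) gives these rejection rates with no true effect. SDs of 24 and 48 are assumed values.

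| Assumed delay | SD 12 | SD 24 | SD 48 |
|---|---|---|---|
| None | 0.051 | 0.050 | 0.050 |
| 24 h in 10% of controls | 0.107 | 0.066 | 0.055 |
| 12 h in 25% of controls | 0.150 | 0.073 | 0.057 |
| 24 h in 25% of controls | 0.364 | 0.149 | 0.076 |
| 24 h in 25% of controls and 10% of the ultrasound arm | 0.147 | 0.084 | 0.059 |
| 24 h in 25% of both arms | 0.049 | 0.050 | 0.051 |

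The Mann-Whitney test, which section 2.13 provides for non-normal data, gives 0.278, 0.134 and 0.070 for 24 h in 25% of controls (8,000 trials, normal data). A right-skewed distribution with SD 12 gives 0.106 and 0.371 under the t-test for 24 h in 10% and 25% of controls.

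Loss of power, with a true effect of 10 h, SD 12 and the 24 h delay in the ultrasound arm only:
- p = 0.10: net difference 10 − 2.4 = 7.6 h. Simulated power is 0.602, against 0.886 with no delay.
- p = 0.25: net difference 10 − 6 = 4 h. Simulated power is 0.203.

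The effect of the MAP ranges alone cannot be quantified from the document.

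**The case against.** Several objections have force.

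- **Disclosure.** The trial is labelled non-blinded, and the limitations call blinding of clinicians impractical. This stands: unblinded care is not concealed. However, the limitation offers only withheld scans as mitigation and does not mention weaning.
- **Times are set.** A reader might infer that the rule has no timing at all. It has three minimums: more than 72 h after birth, over 24 h sustained, and at least 48 h before reassessment. Only a latest time is absent.
- **The MAP range is narrow.** It spans 1 cmH2O, affects the stopping of non-invasive support on NIPPV only, and sits beside fixed limits for FiO2, SAS and pauses. Nothing shows that MAP would be the condition that decides. This stands as a limit on its weight.
- **Assumed magnitude.** A reader might take 36% as the trial's error rate. The document does not support that. The figure needs a 24 h delay in a quarter of controls, none in the ultrasound arm, and SD 12. Nothing in the document shows that clinicians would wean the arms differently.
- **Condensed article.** Decision timing and a field for reasons might sit in a fuller protocol or in the case report forms mentioned in section 2.4. This carries less weight. The article prints the rule in detail, and the ranges and the optional wording are what it fixes. An analysis plan cannot repair a bedside rule.

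Leaving the stop to clinical judgement is also a reasonable safety choice and is not the defect.

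**Conclusion.** The point holds in a limited form. Staff who know the arm decide when the primary outcome ends, the rule leaves them compliant discretion both before and after the conditions are met, and neither stated safeguard acts on that decision. The size and direction of any resulting bias are unknown.

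Under the assumed one-sided delays at SD 12, false positives run from about 11% to 36%, or power falls from about 89% to between 60% and 20%. Equal delay does no harm to the error rate, and larger SDs shrink the inflation. The case for a change rests on the open route into the primary outcome, not on any single figure. This is a worthwhile, inexpensive improvement, not evidence that the trial will be biased.

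**What to change.** Keep observed hours as the primary outcome and keep clinical judgement on stopping.

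1. **One value per pressure limit**, the same in both arms and confirmed clinically: for example PEEP 5 cmH2O or less, MAP below 7 on NIPPV, and MAP below 8 for extubation.
2. **A dated decision.** Replace the optional sentence in section 2.8 with wording such as: *Once all five conditions have been sustained for over 24 h, a stopping decision will be made and documented no later than the next daily round; if support continues, the reason will be recorded.* Report by arm the delay from that documented point to the stop.
3. **Candour on blinding.** Say in section 2.5 and in the limitations that assessor blinding does not cover weaning decisions.

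A supportive outcome of time to first meeting the conditions is tempting but should not be added as things stand. It needs near-continuous bedside data, whereas the assessments in section 2.6 are scheduled at fixed points, and a first time ignores reinstated support, which section 2.8 expects. It becomes an option only if bedside charts are confirmed to hold the data and restarts are handled.

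**Cost.** One short recorded decision per infant, repeated daily while support continues, for 60 infants. Unblinded staff would still set FiO2 and pressures and score SAS, so bias is reduced and made visible, not removed.

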### Outcome measures

2.9

The primary outcome measure for this study is the duration of mechanical ventilation (both invasive and non-invasive) during hospitalization in the ultrasound and control groups. Secondary outcome measures encompass: (1) the utilization rate of PS in both groups; (2) the proportion of infants receiving the first dose of PS early (within 3 h after birth) and the time from birth to the initial PS administration; (3) the oxygen concentration and the worst oxygenation index (OI) at different time points following PS administration; (4) LUS at various intervals following PS administration (at 3 days, 7 days, 14 days, 28 days, and before discharge/at 36 weeks CA; and (5) the incidence rates of major complications in preterm infants such as BPD, intraventricular hemorrhage (IVH), retinopathy of prematurity (ROP), and necrotizing enterocolitis (NEC).

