## Background

1

Neonatal respiratory distress syndrome (NRDS), resulting from a deficiency in pulmonary surfactant (PS), stands as a primary cause of mortality among premature infants. Currently, clinical symptomatology, combined with chest x-rays, constitute the primary diagnostic modalities for NRDS. However, the subjective nature of symptom recognition and the limitations of chest x-rays, including poor sensitivity and specificity along with radiation exposure, pose challenges for clinicians in the early diagnosis of NRDS. In recent years, bedside lung ultrasonography has gained widespread utilization in neonatal intensive care unit (NICU) settings, with numerous studies showcasing its substantial advantages in NRDS diagnosis (1). Consequently, the latest guidelines have recommended the adjunctive use of bedside lung ultrasonography in NRDS diagnosis (2).

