#### Exclusion criteria

2.2.2

Infants who meet any of the following criteria will be excluded: (1) infants who have received PS treatment in the delivery room or external setting after birth; (2) infants with known or confirmed congenital abnormalities, especially cardiopulmonary deformities during diagnosis or treatment; (3) presence of severe complications at birth (severe asphyxia, hemorrhagic shock, pneumonia, pneumothorax, early-onset sepsis, and pleural effusion) or other diseases not caused by PS deficiency; (4) infants who die within 72 h after birth, are transferred to another hospital for surgery, or have incomplete data; and (5) those with families who do not consent to participate in this study.

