### Data collection and diagnoses

2.10

Patient demographic data mainly include: (1) GA, birth weight, singleton or multiple births, sex, prenatal steroid use, mode of delivery, presence of intrauterine distress, and maternal pregnancy complications; and (2) Apgar scores at 1 min, 5 min, and 10 min, as well as umbilical cord blood gas analysis.

Clinical information at each time point (at admission, 1 h after birth, 4–10 h after PS administration, 24 h, 72 h, 7 days, 14 days, 28 days, and before discharge or at 36 weeks CA) include (1) timing, dosage, and method of the initial PS administration; (2) SAS, respiratory machine mode, oxygen saturation index, and FiO_2_ levels at each time point; and (3) LUS at each time point. LUS will collect individual scores for each lung field as well as the total score.

Complications and outcomes: (1) Respiratory complications: this includes the occurrences of infectious pneumonia, pneumothorax, pulmonary hemorrhage, and BPD, along with their severity grading; (2) Cardiovascular complications: specifically, hemodynamically significant patent ductus arteriosus (hsPDA); (3) Other complications in premature infants: these encompass IVH, periventricular leukomalacia, NEC, late-onset sepsis, ROP, intrauterine growth restriction, and more; and (4) Length of hospital stay and associated costs.

BPD diagnosis will adhere to the 2018 National Institute of Child Health and Human Development (NICHD) classification. Diagnosis of hsPDA will rely on clinical signs and echocardiography (20). IVH and white matter injury will be diagnosed via cranial ultrasound, with IVH graded using the Papile classification (21). NEC staging will follow modified Bell criteria (22). ROP diagnosis and staging will be based on fundoscopic examinations conducted by ophthalmologists.

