### Safety procedures

2.11

Throughout the study duration, researchers will continuously monitor all enrolled infants to ensure their safety. Any occurrence of severe or significant adverse events will be promptly reported to the principal investigator for assessment. This study strictly adheres to the principles of human subject protection, and in the event of adverse events, regardless of their association with the study, the trial will be promptly terminated.

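### The primary endpoint, hours of ventilation, is cut short by death, early deaths are excluded after randomisation, and death is not a listed outcome, so a shorter duration cannot by itself be read as benefit

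*Protocol article*

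**What the plan says.** **Primary outcome (2.9).** "The primary outcome measure for this study is the duration of mechanical ventilation (both invasive and non-invasive) during hospitalization". Section 2.12 plans a two-sample t-test on these hours. Section 2.13 uses the t-test for normally distributed data and the Mann-Whitney test otherwise.

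**Exclusions (2.2.2, criterion 4).** The trial excludes "infants who die within 72 h after birth, are transferred to another hospital for surgery, or have incomplete data". Sections 2.3 and 2.7 place randomisation at admission to the NICU ward, which 2.7 expects within 15 minutes for infants who recover well at birth. An exclusion that depends on survival to 72 h is thus applied after randomisation.

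**Where death could have appeared.**
- The complications among the secondary outcomes in 2.9 are "the incidence rates of major complications in preterm infants such as BPD", followed by IVH, ROP and NEC.
- Table 1 (2.6) has no row for death.
- In 2.10 the other complications are described as follows: "these encompass IVH, periventricular leukomalacia, NEC, late-onset sepsis, ROP, intrauterine growth restriction, and more". That list is open-ended but does not name death.
- Section 2.11 says: "Any occurrence of severe or significant adverse events will be promptly reported to the principal investigator for assessment". This is a reporting route, not a comparison between arms.

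**Why death matters here.** The Background says that NRDS "stands as a primary cause of mortality among premature infants", and also that early surfactant lowers mortality. The trial changes how surfactant timing is decided.

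**The concern.** Ventilation hours stop accruing when an infant dies. A total of 80 h can mean an infant weaned at 80 h or one who died on support at 80 h, and the planned comparison treats the two alike if accrued hours are used. If the infant is instead dropped for incomplete data, the death leaves the analysis altogether. Deaths in the first 72 h leave it in any case.

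On the Background's own reasoning, the intervention may affect survival, so deaths need not be balanced between arms. With mortality absent from the outcome list, a report that follows the document could show shorter ventilation in one arm and say nothing of more deaths there. The reverse is also possible. If ultrasound guidance kept some very sick infants alive, their long courses would count against it.

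**Working it through.** **Inputs from the document.** Control mean 96 h and SD 12 h, ultrasound mean 86 h and SD 12 h, alpha 0.05, power 80%, 24 per group before and 30 per group after inflation (2.12).

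**Not in the document, so assumed.** The number and timing of deaths after 72 h. The range used is 1 to 5 excess deaths in one arm of 30, at 72 h or later, in infants supported continuously from birth, so that hours on support equal age at death.

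**Step 1: the plan's own figure.** Normal approximation, two-sided: n = 2 × (1.960 + 0.842)² × 12² / 10² = 22.6, so 23 per group. The noncentral-t calculation gives 23.6, so 24 per group, with power 80.7%. Then 48 / 0.80 = 60. The stated sample size reproduces.

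**Step 2: shift in an arm mean if accrued hours are used.** With k deaths at hour T replacing infants of average duration, shift = k × (T − 96) / 30.

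| Death at T (h) | 1 death | 3 deaths | 5 deaths |
|---|---|---|---|
| 73 | −0.8 h | −2.3 h | −3.8 h |
| 90 | −0.2 h | −0.6 h | −1.0 h |
| 96 | 0 | 0 | 0 |
| 120 | +0.8 h | +2.4 h | +4.0 h |
| 240 | +4.8 h | +14.4 h | +24.0 h |

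For three deaths spread evenly over 73-96 h, the mean time is 84.5 h and the shift is 3 × (84.5 − 96) / 30 = −1.15 h. The sign changes at about 96 h.

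**Step 3: simulation (20,000 trials, 30 per arm, t-test, excess deaths in one arm only).** Recorded hours are the smaller of the infant's own duration and the time of death.

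- *Planning figures, deaths evenly over 72-96 h.* The shift is −0.4 h (1 death), −1.3 h (3) and −2.3 h (5). The chance of a significant result favouring the arm with more deaths rises from 2.5% to 3.5%, 5.8% and 9.6%.
- *Planning figures, but those who die would have needed five times as long (assumption).* Deaths over 72-120 h give no net shift. Deaths over 72-336 h give +3.6 h (1), +10.8 h (3) and +18.0 h (5), so the arm with more deaths looks worse.
- *Long, skewed durations with mean and SD 480 h, and three times as long for those who die (assumption).* Deaths over 72-336 h give −8.6 h (1), −28.2 h (3) and −46.7 h (5), so that arm looks better. Its chance of a significant favourable result is 2.6%, 3.7% and 5.8%.

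**Step 4: the comparator matters too.** The second scenario puts no equally sick infants in the other arm. Suppose instead that the other arm holds three such infants who survive with 5 × 96 = 480 h each. Deaths at a mean of (72 + 336) / 2 = 204 h then give 3 × (204 − 480) / 30 = −27.6 h. The same deaths can move the comparison either way, depending on assumptions that the document does not settle.

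**The case against.** **The scoring rule may exist elsewhere.** A condensed article can leave the handling of late deaths to the full protocol or analysis plan. This stands: the missing rule is not in itself the point. The outcome list and the 72 h exclusion, however, are fixed in this document, and neither brings death into the comparison.

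**Deaths would be known anyway.** The list in 2.10 is open-ended and 2.11 requires severe events to be reported. This stands as far as capture goes. It does not make mortality an outcome compared by arm.

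**A reader might infer that late death always counts as a short duration and so always flatters an arm.** The document does not support this. It nowhere says that accrued hours are used, and the incomplete-data exclusion might remove the infant instead, which is a different bias. Even with accrued hours, on the planned 96 ± 12 h only deaths between 72 h and about 96 h lower the arm mean. The counter-argument is that death can only shorten a given infant's own course, which is true. But the comparison is between arms, and the sign depends on the other infants and on whether harm prolongs support before death.

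**A reader might extend the point to BPD**, on the ground that an infant who dies before 36 weeks cannot be counted as a case. Section 2.10 refers to a cited classification that is not shown, so this cannot be checked here.

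**A reader might want ventilator-free days to 36 weeks CA or discharge as a new primary endpoint.** That window is not of fixed length. It varies with gestational age at birth and with the date of discharge. The change would also void a sample size that cannot be redone without a mortality rate.

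**Conclusion.** The point holds in limited form. The primary endpoint is truncated by death, deaths within 72 h are removed after randomisation, and all-cause death is not a listed outcome. The comparison can be biased in either direction, including in favour of an arm with more deaths, so a shorter duration cannot be read as benefit without mortality beside it.

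On the planning figures the size is modest: about −1.2 h for three excess deaths at 73-96 h, and upward shifts for later deaths on support. The larger shifts in either direction rest on assumed courses well above 96 h or on deaths well after 96 h. All of these figures assume that accrued hours are analysed and that the excess deaths fall in one arm. This is a reason to add mortality and a supporting analysis. It is not a reason to replace the primary endpoint.

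**What to change.** 1. In 2.9, add all-cause in-hospital death, to discharge or 36 weeks CA, by arm as a secondary outcome in all randomised infants. Count deaths within 72 h, whatever 2.2.2 does with them for the primary analysis.
2. Pre-specify a Mann-Whitney analysis of ventilation hours in all randomised infants, with death before discharge or 36 weeks CA given the worst rank. Require it to agree in direction with the primary result before benefit is claimed.
3. Describe hours in survivors separately, by arm.

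**Cost.** Some outcome wording and a little more analysis. Vital status in hospital is already known, and 2.13 already provides for the Mann-Whitney test. The primary endpoint and the total of 60 stay as they are. The 10 h planning statement then applies only to the unranked hours. No power can be given for the ranked analysis without a mortality rate, which the document does not supply.

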#### Ultrasound group

2.7.1

Lung ultrasonography will be performed within 1 h of admission, followed by lung ultrasound scoring (refer to Figure 2 for the segmentation and scoring methods). In the case of different score patterns in the same area, the worst will be selected. If the lung ultrasound confirms RDS and LUS is more than 8, a full dose of PS will be promptly administered at 200 mg/kg (Poractant Alfa, Curosurf®). If the lung ultrasound does not indicate RDS or if LUS is 8 or less, clinical monitoring will continue. Should the clinical criteria for NRDS be met, a full dose of PS will be administered at 200 mg/kg (Poractant Alfa, Curosurf®). In terms of the administration method, less-invasive surfactant administration (LISA) will be employed for infants in a non-invasive ventilation state, while those in an invasive ventilation state will receive PS via endotracheal tube. Lung ultrasound and scoring will be repeated 4–10 h post the first PS dose administration (with scoring results withheld from the clinical team). Repeated PS administration will occur if the criteria are met, with lung ultrasound scoring conducted prior to each administration (with scoring results withheld from the clinical team). Repeated PS administration will be completed via endotracheal tube.

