#### Control group

2.7.2

In cases where clinical diagnosis confirms NRDS, PS will be administered at a dosage of 200 mg/kg (Poractant Alfa, Curosurf®). LISA will be employed for infants in a non-invasive ventilation state, while those in an invasive ventilation state will receive PS via endotracheal tube. If clinical manifestations do not meet the diagnosis of NRDS, PS will not be administered.

All enrolled infants will undergo lung ultrasound scoring at 24 h, 3 days, 7 days, 14 days, 28 days, and 36 weeks CA (prior to discharge) (with scoring results withheld from the clinical team).

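### Oxygenation after surfactant and time to first surfactant exist only for treated infants, and the two arms select those infants by different rules

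*Protocol article*

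**What the plan says.** The section Outcome measures lists three secondary quantities that depend on surfactant (PS) having been given:

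- Outcome 2 includes the interval from birth to the first dose, next to the proportion dosed within 3 h.
- Outcome 3 is "the oxygen concentration and the worst oxygenation index (OI) at different time points following PS administration". No postnatal ages are attached to it.
- Outcome 4 is "LUS at various intervals following PS administration", followed by a list of ages: 3, 7, 14 and 28 days and discharge or 36 weeks corrected age.

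The arms reach PS by different routes. In the ultrasound group, PS is given when ultrasound confirms RDS and the lung ultrasound score (LUS) is above 8. If that is not so, monitoring continues and a second route stays open: "Should the clinical criteria for NRDS be met, a full dose of PS will be administered". The control group has the clinical route only: "If clinical manifestations do not meet the diagnosis of NRDS, PS will not be administered".

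The section Control group also says that every enrolled infant is scored for LUS at 24 h, at 3, 7, 14 and 28 days, and at 36 weeks. Table 1 and Data collection and diagnoses place most measurements at postnatal ages; the 4–10 h point is the only one tied to PS. For continuous data, Statistical analysis offers a t-test or a Mann-Whitney test.

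**The concern.** Whether and when an infant receives PS is decided after randomisation, and it is exactly what the two strategies change. A comparison that starts at PS administration keeps only the treated infants in each arm, and randomisation no longer makes those subsets comparable.

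The difference has a structure. The ultrasound arm's rule is the control arm's rule plus an extra way in. Its treated set therefore holds the kind of infant the control arm would treat, plus infants with RDS and LUS above 8 who would never have met the clinical criteria. Those criteria rest on worsening signs, saturation, the Silverman Anderson score and FiO2, which are close to what outcome 3 measures. On that scale the added infants are milder, so better oxygenation after PS could appear in the ultrasound arm without any benefit from the strategy. The clocks can also differ: control infants must worsen before dosing, so a given number of hours after PS may fall at different postnatal ages in the two arms.

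Time to first PS has a related problem. An untreated infant has no value, and neither a t-test nor a Mann-Whitney test on the observed times can take that infant into account.

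**Working it through.** **1. The plan's own figure.** The only calculation in the document is for the primary outcome: "an average of 96 ± 12 h of respiratory support" against "reducing the mechanical ventilation duration to an average of 86 ± 12 h", α 0.05 (two-sided assumed), power 80%. The normal approximation gives 2 × (1.960 + 0.842)² × (12/10)² = 22.6, so 23 per arm. With the noncentral t, power is 0.789 at 23 and 0.807 at 24, which agrees with "each group will require 24 patients, totaling 48 patients". Then 48 / 0.80 = 60. This reproduces and is not touched by the present point. The document gives no figure for the secondary outcomes.

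**2. The treated sets.** Let C be the infants who would meet the clinical criteria and L those with RDS and LUS above 8.

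- Control arm treated: C.
- Ultrasound arm treated: C or L, that is, C plus those in L but not in C.

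The added infants all lie below the clinical threshold, so the mean clinical severity of the treated ultrasound infants is at most that of the treated controls.

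**3. Size, under assumptions.** I simulated 30 infants per arm with no effect of arm or PS on anything. Clinical severity S and ultrasound severity were standard bivariate normal with correlation ρ. Assumed ranges were:

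- control PS rate 40, 51 or 70%. The 51% is the starting likelihood of PS that Background reports for a cited cohort, not for this trial;
- share with LUS above 8 (taken to include confirmed RDS) 40, 51 or 65%;
- ρ from 0.3 to 0.9;
- later measurement correlated 0.8 with baseline severity.

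One case by hand, with control PS rate 51%, LUS share 51%, ρ = 0.5. Treated controls have mean S = φ(z)/p = 0.399/0.51 = 0.78. The ultrasound arm treats 68%. The simulated mean of its treated infants is 0.44, which implies a mean of (0.68 × 0.44 − 0.51 × 0.78)/0.17 = −0.58 in the added 17%. The gap is about −0.35 SD after rounding.

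Selected cases (differences are ultrasound minus control among treated infants; false-positive rates are two-sided at 5%):

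| Control PS | LUS > 8 | ρ | Ultrasound PS | Difference in clinical severity (SD) | False positives, oxygenation | Difference in LUS severity (SD) |
|---|---|---|---|---|---|---|
| 70% | 40% | 0.9 | 70% | −0.01 | 5.0% | 0.00 |
| 51% | 40% | 0.9 | 54% | −0.06 | 5.2% | −0.01 |
| 51% | 51% | 0.5 | 68% | −0.35 | 14.8% | +0.05 |
| 51% | 65% | 0.3 | 78% | −0.53 | 27.5% | +0.07 |
| 40% | 40% | 0.3 | 59% | −0.48 | 18.9% | +0.20 |
| 40% | 65% | 0.9 | 66% | −0.45 | 19.9% | −0.31 |
| 40% | 65% | 0.3 | 75% | −0.71 | 38.2% | +0.08 |

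The severity gap is at baseline. In the later measurement it shrinks by the assumed correlation, for example 0.8 × 0.71 = 0.57 SD.

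**4. The same data, all randomised infants.** Comparing all 30 per arm gave false-positive rates of 4.1% to 5.6% across the grid. With 2,000 replications the Monte Carlo standard error is √(0.05 × 0.95/2000) = 0.5 percentage points, so this is nominal.

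**5. LUS.** The treated-only difference runs from −0.31 to +0.20 SD, with false positives of about 4% to 12%. The sign is not fixed, because the added infants have high LUS by definition.

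**The case against.** The strongest reply is that the document nowhere says that untreated infants are left out. FiO2 and LUS are scheduled at postnatal ages for everyone, analysis sets are often left to a fuller plan, and the outcome wording may simply be loose. The PS utilisation rate and the proportion dosed within 3 h are defined for every infant and already show whether PS is given more often and earlier.

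Much of this stands. The restriction is an inference from the wording. For outcome 4 it is a weak one, because the listed ages are those at which every enrolled infant is scored; that is an internal inconsistency to reconcile, not an established treated-only comparison. For outcome 3 and for time to first PS, however, the definition itself is anchored to PS and no other reading is offered, so the fault lies in the outcome and not in omitted analysis detail.

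Three stronger readings are tempting and not supported:

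- A reader might infer that LUS after PS would also look spuriously better in the ultrasound arm. The added infants are milder on the clinical scale but have LUS above 8, so the direction can go either way.
- A reader might infer that the bias in oxygenation must be material. It is close to zero when LUS and clinical severity agree closely and the control PS rate is high.
- A reader might infer that the trial's main result is compromised. Only secondary outcomes are involved.

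**Conclusion.** The point holds for outcome 3 and for time to first PS. Both are defined only for infants who receive PS, and the arms trigger PS by different rules. On the clinical scale the treated ultrasound infants are, at least weakly, the milder group, so a treated-only comparison of oxygenation can favour ultrasound with no true effect.

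The size is unknown because the document gives no PS rates for this trial and no correlation between LUS and clinical severity. Under the assumed ranges the severity gap is 0.01 to 0.71 SD and the false-positive rate about 5% to 38%; at a 51% control PS rate these are 0.06 to 0.53 SD and about 5% to 28%. No size or direction was computed for time to first PS.

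For outcome 4 the conclusion is limited to the conflict between its wording and the all-infant LUS schedule.

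**What to change.** - **FiO2 and LUS:** define them at the fixed postnatal ages already in Table 1 and Data collection and diagnoses (24 h; 3, 7, 14 and 28 days; 36 weeks corrected age or discharge), for all randomised infants whether or not they received PS. Remove the reference to PS from outcome 4 so that it agrees with the Control group section.
- **Worst OI:** define it (or the saturation-based index named in Data collection and diagnoses) over a fixed postnatal window for all randomised infants in whom it is collected.
- **Timing of first PS:** compare it over all randomised infants as cumulative incidence from birth, with untreated infants censored at a fixed, prespecified hour, alongside the proportion treated within 3 h that is already listed.
- **Summaries by hours after PS, or in treated infants only:** keep them, labelled as descriptive.

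The cost is a change of wording and slightly more analysis. LUS and FiO2 are already scheduled at these ages. OI may not be available at every age: Table 1 has no row for it. The primary outcome and the 60-infant sample size do not change.
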